### Study population

Adults (age > 18 years) capable of utilizing the kiosk who have self-reported histories of hypertension and present with uncontrolled BP to the ED (>140/90 for non-diabetics and >130/80 for diabetics) will be targeted for recruitment. ED staff, familiar with the study eligibility criteria, will provide initial screening to identify potential study participants. As primary exclusion criteria, those patients with a diagnosis of end-stage renal disease, cognitive impairment, or requiring hospitalization after ED discharge will not be eligible for study participation.

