**Fig. 3 Fig3:**
[figure not shown]
Anti- hypertensive regimen. Note: Medications are prescribed in the absence of any contraindications

The study will be conducted by a multi-disciplinary team of trained emergency clinical medicine and public health researchers in two urban health environments: an emergency department and an academic clinical research center. Under the supervision of a research physician, patient screening, enrollment, baseline assessment and the first education intervention will be conducted by research assistants at the emergency department. The research physician will then review medication orders and provides instructions for the participant at enrollment. All subsequent study visits will occur at the clinical research center (CRC) about one mile away. At the beginning of each visit, the research physician and his clinical research team will review medication side effects, conduct pill counts and provide medication refills at seven, thirty and ninety day visits, with a three month prescription at the 180 day follow-up. Graduate level public health students will conduct post and follow-up interviews and facilitate patient education for the intervention group.

To promote retention, reminder calls and/or email will be done several days in advance and contact information will be updated at each visit. Both groups will be encouraged to monitor their blood pressure on their own and follow-up with a primary care physician. Participants missing visits and not responding to up to three reminder communication will be considered lost to follow-up. Participants will be withdrawn from the study for reasons such as withdrawing consent or moving too far away.

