### Statistical analysis

The OnCore Clinical Trial Data Management System, which is internet accessible and HIPAA compliant, will be used for protocol management & data entry. Primary analyses will be conducted using IBM SPSS (v. 20). Initial analyses will consist of descriptive statistics including univariate and bivariate frequency distributions. Differences in baseline socio-demographic and medical variables between the two groups will be used as covariates if appropriate statistical assumptions are met. Tests of the hypotheses will use the intent to treat analysis and all available outcome data.

To assess if the intervention improves blood pressure control over standard discharge practices, differences between groups will be assessed using blood pressure as a continuous variable (i.e., changes in systolic/diastolic readings) and as a dichotomous variable (i.e., number of patients with controlled blood pressure.

A generalized linear mixed model analysis will be used to test differences between groups over time, using continuous blood pressure measures. Both groups are expected to show decreases in blood pressure over time but with greater decreases for the intervention group. Thus, for the continuous blood pressure measures, the major effect of interest will be the linear group x time interaction. We assume that decreases in blood pressure over the time periods will be roughly linear, although a quadratic time effect may also occur. Based on a standard deviation of 12 mmHg for systolic blood pressure, a clinically relevant decrease of 6 mmHg systolic blood pressure (i.e., d = .5), and a one-sided alpha of .05, the study will have adequate power (.80) with 50 subjects in each group. This is a somewhat conservative estimate which does not take into account repeated measures, blocking, or possible covariate adjustments, all of which would tend to increase power.

Group differences in decreased percentages of those with uncontrolled blood pressure will be compared at each time point. Percentages will be compared using the arc sine transformation. For power assessment, we assume a medium effect size of h = .5 [45], where h is the difference between arc sine values for the population proportions of the two groups. Illustrative pairs of proportions for h = .5 are 60–35, 65–40, 69–45, and 79–50. For these effect sizes, *n* = 50, and a one-sided alpha of .05, power would be .80. General linear models will be used to test the full range of assessment periods.

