
In addition to assessing the primary outcome, the project will assess two secondary hypotheses related to patient activation. Analysis of covariance using the baseline activation score as covariate will be conducted to test for significant differences in patient activation scores between groups at the 180 day assessment. Pearson correlations and subsequent multiple regression analyses will test the association between patient activation scores and engaging in self-monitoring of blood pressure, medication adherence scores, demographics, and number of subsequent emergency department and primary care visits. Logistic regressions will explore differences in participant study completion and in obtaining BP control.

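### BP control across visits is assigned a normal-error linear model, and the per-visit percentages make no use of interim BP when day-180 readings are missing

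*Protocol article*

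**What the plan says.** The Abstract of the Protocol article makes BP control at 180 days the primary endpoint. Study outcomes adds the difference in actual readings. Study design and aims lists outcome assessments at baseline and at 30, 90 and 180 days.

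The Statistical analysis section treats the two forms of the outcome differently:

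- Continuous BP: "A generalized linear mixed model analysis will be used to test differences between groups over time, using continuous blood pressure measures".
- Controlled/uncontrolled, visit by visit: "Group differences in decreased percentages of those with uncontrolled blood pressure will be compared at each time point", with the method "Percentages will be compared using the arc sine transformation".
- The paragraph on percentages then closes with: "General linear models will be used to test the full range of assessment periods".
- Logistic regression appears only in an exploratory role: "Logistic regressions will explore differences in participant study completion and in obtaining BP control".

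On the data to be analysed, the section states: "Tests of the hypotheses will use the intent to treat analysis and all available outcome data". Consent and Randomization enrols 100 per arm to allow for attrition, while the power statements need 50 per arm. On loss, Study procedures says: "Participants missing visits and not responding to up to three reminder communication will be considered lost to follow-up".

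**The concern.** Read in its paragraph, the closing sentence puts a general linear model (normal errors, common variance) on a binary outcome measured repeatedly in the same people. The model family that would suit that outcome is named in the same section, but only for continuous BP.

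The second issue is missing outcomes. A percentage computed at one visit can use only people with a reading at that visit. It makes no use of what was measured at days 30 and 90 in someone with no day-180 reading. With up to half of the outcomes allowed to be missing, the primary proportion could be biased if loss is related to BP and differs between arms. The design makes this plausible. Study medication is supplied at the clinic visits, so people who stop attending also lose their supply, and only the intervention arm has kiosk sessions at those visits.

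**Working it through.** **1. The plan's own figure.** Inputs (Statistical analysis): h = 0.5, n = 50 per arm, one-sided alpha 0.05. Power = Φ(h√(n/2) − 1.645) = Φ(0.5 × 5 − 1.645) = Φ(0.855) = 0.80. The stated power reproduces, and it rests on the arcsine comparison at a single visit.

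**2. Variance at baseline.** Eligibility needs BP above 140/90 (130/80 for diabetics), re-checked before randomization. Control means at or below the same limits. The proportion p controlled at baseline is therefore close to 0 in both arms. The variance p(1 − p) is close to 0 there, against 0.45 × 0.55 = 0.25 at a visit with 45% control. Common variance over the full range of visits cannot hold.

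**3. Does this distort the tests?** One-sided type I error with 50 per arm and equal true rates:

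- Arcsine test at one visit, exact, p from 0.20 to 0.65: 0.045 to 0.054.
- Linear-model t test at one visit, exact: 0.045 to 0.051.
- Repeated-measures linear group-by-time contrast including an all-uncontrolled baseline, simulated: about 0.052 with its own error term and 0.055 with pooled error.

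The assumption fails, but the error rate barely moves.

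**4. Room for missing outcomes.** 50 of 100 per arm means up to 50% loss. Oversampling by 50% taken literally would be 50 × 1.5 = 75 per arm, or a loss of one third.

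**5. Loss that depends on interim BP (assumed rates, no true effect).** Suppose 40% are controlled at day 90 in both arms. Day-180 control is 65% in those controlled at day 90 and 25% in the others, so true day-180 control is 0.4 × 0.65 + 0.6 × 0.25 = 0.41. In the kiosk arm, day-180 attendance is 75% if controlled at day 90 and 35% if not. In the control arm it is unrelated to BP.

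- Kiosk-arm retention: 0.4 × 0.75 + 0.6 × 0.35 = 0.51, taken as 51 per arm in both arms.
- Observed kiosk-arm control: (0.30 × 0.65 + 0.21 × 0.25)/0.51 = 0.485, against 0.41 in the control arm.
- h = 2asin√0.485 − 2asin√0.41 = 0.152. Rejection rate: Φ(0.152 × √(51/2) − 1.645) = Φ(−0.88) = 0.19.
- Using day-90 status: weighting the kiosk-arm strata back to 40/60 gives 0.4 × 0.65 + 0.6 × 0.25 = 0.41, equal to the control arm. Simulated error is about 0.05.

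With the day-90 to day-180 link weaker (60% v 27%) or stronger (70% v 20%), the available-case error is about 0.16 or 0.25. About 0.20 is a fair central value.

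**6. Loss that depends on the day-180 result itself (assumed rates).** True control is 40% in both arms. Kiosk-arm retention is 60% of controlled and 40% of uncontrolled; control-arm retention is 48% regardless.

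- Kiosk-arm retention: 0.4 × 0.6 + 0.6 × 0.4 = 0.48. Observed control: 0.24/0.48 = 50% v 40%.
- h = 0.201; error Φ(0.201 × √(48/2) − 1.645) = Φ(−0.66) = 0.26.
- Counting missing as uncontrolled: 0.24 v 0.4 × 0.48 = 0.192 of 100 per arm; h = 0.117; error Φ(0.117 × √50 − 1.645) = 0.21.

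**7. Power if missing is counted as uncontrolled (50% loss, 100 per arm).** Each proportion is halved. The article's illustrative pairs give 0.67 (60–35), 0.65 (65–40), 0.60 (69–45) and 0.71 (79–50). The same pairs give 0.81, 0.81, 0.79 and 0.93 with 50 analysed per arm.

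**The case against.** The primary endpoint is a single time point, and the arcsine comparison there is a valid two-sample test that matches the power basis. This stands, so the test can be kept for day 180. The sentence on general linear models may also be a slip for generalized, and it concerns the analysis across visits. That is possible, but the sentence still needs correcting.

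Four stronger readings are tempting, and the documents do not support them:

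- **That standard errors or tests are shown to be wrong.** Step 3 shows near-nominal error.
- **That many participants will be deleted listwise because SPSS is named.** The article names the package, not a procedure, and says all available outcome data will be used.
- **That the plan contradicts intent to treat.** Analysing available readings by randomized arm does not in itself do so, and a rule for missing outcomes may stand in a full protocol or SAP not shown here.
- **That one missed visit ends follow-up.** The loss rule also requires no response to the reminders.

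Two further cautions are fair. Baseline control is not forced to be exactly 0%, because baseline assessments follow randomization and the BpTRU device may read differently from the screening readings. And the bias figures are constructed: with loss unrelated to outcome the error stays at 0.05.

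**Conclusion.** The point holds in limited form, as a should-fix. The article assigns a general linear model to repeated binary BP control, where a binomial/logit model is the natural choice and is already within the methods it names. The fault is one of model choice; no material inflation of type I error from it has been shown.

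The missing-outcome part is conditional. If loss depends on BP and differs by arm, day-180 percentages among those with a reading can carry a one-sided error of about 0.20 (range 0.16 to 0.25 in step 5), and use of interim BP brings it back to about 0.05. This rests on the assumed attendance and control rates and on reading 100 enrolled for 50 needed as up to 50% loss. Where loss depends on the unseen day-180 value (step 6), neither imputation from earlier visits nor counting missing as uncontrolled can be relied on to remove the bias. That is the reason to pursue the reading itself.

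**What to change.** 1. Replace the sentence on general linear models. Analyse BP control at days 30, 90 and 180 with a generalized linear mixed model with binomial/logit link, or a logistic GEE combined with multiple imputation. Include arm, categorical visit, arm by visit, diabetes stratum and baseline systolic BP, with the day-180 arm contrast as the primary one.
2. Keep the arcsine test, if wanted, as the simple day-180 comparison and as the power basis.
3. Bring interim BP into the day-180 result through the model or through multiple imputation by arm.
4. Add one sensitivity analysis counting a missing day-180 result as uncontrolled. Do not make it primary: it lowers power (step 7) and does not remove the bias in step 6.
5. State that a day-180 BP will be sought from everyone who has not withdrawn consent, including people classed as lost at an earlier visit.

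The cost is a few sentences of protocol text, modest extra analysis and a few reminder calls near day 180.

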## Discussion

Persistently elevated BP is a leading risk factor for cardiovascular disease development, making effective hypertension management a critical public health issue. Emergency departments have limited resources for chronic disease management, especially for underserved patients dependent upon the ED for primary care. Kiosk-based patient education has been found to be effective in primary care settings, but little research has been done on the effectiveness of interactive patient education modules as part of the ED discharge process.

The AchieveBP trial will determine whether using kiosk-based patient education as ED enhanced discharge with follow-up at a clinical research center is an effective strategy for achieving short-term patient management of BP. The project is innovative in that it uses the ED as a point of service for kiosk-based health education designed to increase BP self-management. It is anticipated findings from this translational research could also be used as a resource for health education and follow-up with hypertensive patients in primary care settings.
